### Sample size considerations

The statistical power of the study was calculated for the primary endpoint (five-year freedom from biochemical failure). Based on data of two randomized clinical trials [2,51] reporting the treatment results of patients treated with a radiation dose equal to the dose of the standard arm of our trial, we expect that the five-year freedom from biochemical failure of the standard arm will be approximately 64%. We expect that an additional ablative microboost to the macroscopic tumor will increase this number with at least 10%. A one-sided log rank survival power analysis shows that the length of follow-up after accrual of the last patient should be 3.5 years to detect a difference of 10% (64% and 74% free from biochemical failure after 5 years, in the control arm and experimental arm, respectively) with a power of 80% at a one-sided 5% significance level. This is under the assumption that the patients enter the study during an accrual period of 5 years, 50% of the enrollment is complete when 70% of the accrual time has past and that 20% of the patients in both arms are lost to follow-up during the follow-up period of 5 years. The reason to choose a one sided p-value is that, although extremely improbable, an increase in biochemical failure in the experimental arm would lead to the same action as no difference at all between the two treatment arms. This is because the experimental treatment will only be implemented if it is significantly better than the usual treatment, due to the increased toxicity risk in the experimental arm.

### Data analysis

All analysis will be performed according to the intention-to-treat principle. Cox proportional hazards regression will be used to analyze differences in biochemical failure and disease-specific survival between the two treatment arms. Survival curves will be estimated by the Kaplan-Meier technique. Differences between both groups in the incidence of acute side-effects will be tested with the Chi square test. The incidence of late toxicity will be analyzed actuarially with the Kaplan-Meier method, the log rank test and Cox regression analysis. To analyze differences in QoL between the two treatment groups over the time points, a general linear model repeated-measures analysis of covariance will be performed [52]. A change of 10% (or in general, 0.5 standard deviation) of the scale width is perceptible to patients as a meaningful change [53]. Because of the multiple comparisons for the QoL items, the p-value is set at a conservative 0.01 for determining statistical significance [54]. For all other analyses, which do not include the QoL measures, a p-value of < 0.05 is considered statistically significant.

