## Methods/Design

### Study design

The FLAME-trial is a multicenter randomized controlled trial. Patients are recruited during the intake consultation at the Department of Radiation Oncology in one of the participating centers. After giving informed consent, patients are randomized either to the standard arm or to the experimental arm. Patients in the standard arm receive radiotherapy according to the current standard [4], namely 77 Gy in 35 fractions of 2.2 Gy to the whole prostate. Patients in the experimental arm receive an additional integrated microboost to the macroscopic tumor to a total dose of 95 Gy in 2.7 Gy fractions.

To ensure unbiased assessment of QoL measurements, the patients are blinded to the actual treatment given (receiving an ablative microboost or not). The treating physician needs to be informed about the actual treatment, to be able to judge the treatment plans. This is unlikely to influence the assessment of the objective primary endpoint of the trial.

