### Radiotherapy

To minimize the positioning errors during treatment all patients are treated with an online position verification protocol using implanted fiducial gold markers [14,31,32]. Radiotherapy will be delivered with advanced radiotherapy techniques to be able to create adequate dose distributions.

A mean dose of 77 Gy in 35 fraction of 2.2 Gy is prescribed to the entire prostate gland [33,34]. The dose in the part of the PTV overlapping the rectum and bladder is limited to keep the risk of severe gastrointestinal and genitourinary toxicity acceptable.

To provide an accurate delineation of the prostate gland with respect to the surrounding tissues [35,36], the prostate is delineated on a computed tomography (CT) scan combined with a registered magnetic resonance imaging (MRI) scan. The rectum is contoured from the anus or ischial tuberosities to the rectosigmoid flexure or sacroiliac joints. The bladder is completely outlined from the bladder neck to the dome.

The precise execution of the radiotherapy treatment can differ in each participation center, but the treatment will always meet the above mentioned criteria.

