### Safety

An independent data safety monitoring board (DSMB) will evaluate the toxicity and clinical outcome. The DSMB receives an update of the toxicity in total and per treatment arm every 3 months. Serious toxicity, defined as any acute or late toxicity requiring surgical intervention, any grade 4 toxicity, and any not-transient (duration >6 months) late toxicities grade 3, will immediately be reported to the DSMB. An overview of the percentage of biochemical recurrences per treatment arm together with the evaluated number of patients per arm will be sent to the DSMB yearly as well as a statistical comparison of the incidence of serious and less serious toxicities in the two arms. The DSMB decides on stopping or continuing the trial. Exact rules cannot be specified in advance, but an increase in the incidence of toxicity (grade 3-4) with 5% or a smaller, but statistically significant increase, are among the reasons to consider stopping the trial. The DSMB can decide to prematurely stop the trial in case the improvement in the experimental arm is higher than anticipated in the trial design.

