## Discussion

The FLAME-trial is designed to investigate the effect of an ablative microboost to the macroscopic tumor for patients treated with external beam radiotherapy for prostate cancer.

Previous studies demonstrated that the rate of toxicity after high dose external beam radiotherapy with the use of accurate position verification is low and consequently high QoL is reported [34,63-66]. Planning studies showed that an ablative microboost to the macroscopic tumor was theoretically feasible within the currently used dose constraints for rectum and bladder [15,67,68]. Furthermore, a feasibility study of Singh *et al*. [20] reported excellent early toxicity after simultaneous integrated IMRT boost of 95 Gy to the intraprostatic lesions. As a result, with the use of optimal position verification combined with the currently used dose constraints, the toxicity in the experimental treatment arm with the ablative microboost of 95 Gy is expected to be acceptable.

Previous trials demonstrated a biochemical benefit of dose escalation. However, up to now none of the dose escalation trials were able to detect an improvement in disease specific or overall survival. However, all trials were designed for biochemical survival instead of overall or disease-specific survival due to the natural behavior of prostate cancer. For this reason the FLAME-trial is also powered for biochemical disease free survival. An improvement in local control without a proven benefit in overall survival is only acceptable when severe toxicity remains limited. Furthermore, to establish whether a benefit in biochemical failure free survival also counterbalances the negative aspects of dose escalation, such as a small increase in toxicity, it is important that QoL is taken into account. Therefore, repeated QoL measurements are performed in patients included in this trial.

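### Toxicity is analysed by intention to treat only; adding a treatment-received analysis would guard against experimental-arm patients without a boost diluting the harm estimate

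*Protocol article*

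**What the plan says.** The Data analysis section opens with a rule that has no exceptions: "All analysis will be performed according to the intention-to-treat principle". The toxicity tests follow in the same paragraph. For acute effects: "Differences between both groups in the incidence of acute side-effects will be tested with the Chi square test". For late effects: "The incidence of late toxicity will be analyzed actuarially with the Kaplan-Meier method, the log rank test and Cox regression analysis". Outside quality of life, "a p-value of < 0.05 is considered statistically significant"; whether the toxicity tests are one- or two-sided is not stated. No safety population or treatment-received comparison is named.

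On the order of events, the Study design section says: "After giving informed consent, patients are randomized either to the standard arm or to the experimental arm". The Patients section lists eligibility and exclusion criteria, and none of them requires a tumour that can be seen on MRI. The Intervention section makes MRI delineation of the tumour the basis of the boost.

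Toxicity carries weight in the conclusion. The Discussion says that better local control without a proven survival gain "is only acceptable when severe toxicity remains limited". The Safety section names, among the reasons to consider stopping, "an increase in the incidence of toxicity (grade 3-4) with 5% or a smaller, but statistically significant increase".

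**The concern.** ITT is the cautious choice for an efficacy claim, because patients who do not get the experimental treatment pull the arms together. For harm the same pull is the lenient direction. A man randomised to the boost but treated only with the whole-gland dose is counted as a boosted patient, and his toxicity is averaged into the boost arm.

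The design leaves room for this: allocation comes after consent, with no prior planning scan or delineable lesion named as a condition. The trial's own argument for adopting the boost depends on severe toxicity staying limited, so a harm estimate that can only be diluted deserves a second view. Because the ITT rule is stated for every analysis, this is something the article fixes, not a detail it leaves open.

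**Working it through.** **The plan's own figures.** The article gives no power for toxicity and no expected toxicity rate. Its one power figure, 80% for the primary endpoint, reproduces: 566 patients give about 163 expected events and one-sided power of 80.6% (Schoenfeld) or 79.7% (Freedman). The present point does not affect it. Only the 283 per arm is carried forward.

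**Inputs.**
- n = 283 per arm (Abstract).
- Significance level 0.05 (Data analysis); two-sided is an assumption.
- True excess in boosted patients of 5 percentage points: an assumption, chosen to match the 5% in the Safety section read as an absolute increase.
- Standard-arm risk p0 of 5%, with 3% and 10% as a range: assumptions.
- f, the share of the experimental arm given no boost, of 5%, 10% or 20%: assumptions.
- Unboosted patients have risk p0, and boosted patients are otherwise like the rest of their arm: assumptions.

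**Dilution.** With p1 the risk when boosted, the ITT risk in the experimental arm is f·p0 + (1 - f)·p1. The ITT difference is therefore (1 - f)(p1 - p0).
- f = 5%: 0.95 × 5 = 4.75 points
- f = 10%: 0.90 × 5 = 4.5 points
- f = 20%: 0.80 × 5 = 4.0 points

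In patients, the full excess is 283 × 0.05 = 14.15 events. The number lost is 283 × 0.05 × f, which is about 0.7, 1.4 or 2.8 events.

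**Power.** Two-proportion normal approximation with difference d:

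power = Φ{[d - 1.96·√(p̄(1 - p̄)(1/n0 + 1/n1))] / √(p0(1 - p0)/n0 + p1(1 - p1)/n1)}

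where p̄ is the pooled risk. For ITT, n0 = n1 = 283 and the diluted experimental-arm risk replaces p1. For boosted patients against the standard arm, n1 = 283(1 - f) and d stays at 5 points; unboosted men are left out of that comparison.

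Example, p0 = 5%, f = 10%:
- ITT: 5% v 9.5%, (0.045 - 1.96 × 0.02180)/0.02172 = 0.105, so power is 54%.
- Boosted only: 5% v 10%, n1 = 254.7, (0.05 - 1.96 × 0.02256)/0.02283 = 0.253, so power is 60%.

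| p0 | Full delivery | ITT, f = 5 / 10 / 20% | Boosted v standard, f = 5 / 10 / 20% |
|---|---|---|---|
| 3% | 74.3% | 70.8 / 67.1 / 58.9% | 73.4 / 72.5 / 70.5% |
| 5% | 61.8% | 58.0 / 54.2 / 46.2% | 60.9 / 60.0 / 57.9% |
| 10% | 43.6% | 40.3 / 37.1 / 31.0% | 42.8 / 42.1 / 40.4% |

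The fair measure of what the analysis rule costs is the gap between the last two columns, because no rule restores full delivery. At p0 = 5% the gap is about 3, 6 and 12 percentage points (60.9 - 58.0, 60.0 - 54.2, 57.9 - 46.2).

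The calculation applies directly to the acute chi-square test. For the late-toxicity log-rank and Cox analyses the direction is the same, but the exact figures would differ. All figures describe a final comparison on complete data, not interim looks.

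**The case against.** The strongest reply is that non-delivery is assumed. The article gives no rate, and its Discussion reports that a high dose to the tumour proved achievable within the organ constraints in the first 50 patients. That stands: only the possibility of non-receipt follows from the text, not its frequency.

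A reader might go further and infer that the article itself foresees omitted boosts. The Radiotherapy section says that "The dose in the part of the PTV overlapping the rectum and bladder is limited", and the Discussion mentions conflicting images. Neither supports that reading. The dose limit is part of the general technique for both arms and does not say that a boost is left out. The imaging remark concerns where the edge of the tumour lies, which presupposes a visible tumour.

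A reader might also treat the 5% in the Safety section as a fixed trigger that dilution pushes out of reach. It is not one. That section says exact rules cannot be set beforehand, offers 5% as one consideration, and puts a smaller significant increase beside it. Serious toxicities also reach the DSMB at once, whatever the analysis set.

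Finally, ITT for toxicity is a legitimate choice. It weighs benefit and harm in the same randomised groups. If men go without a boost because of their anatomy, removing them from their arm introduces confounding of unknown direction. This stands too, and it rules out making treatment received the lead analysis.

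One reply does not stand: that the matter belongs to an unseen analysis plan. A condensed article may leave supplementary tables to such a plan, but here it states a rule for all analyses, and on its face that rule covers harm.

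**Conclusion.** The point holds as a modest improvement, not as an error that endangers the trial. The stated rule puts every toxicity comparison under ITT, which is the lenient direction for harm if any experimental-arm patients go unboosted and carry standard-arm risk.

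On an assumed 5% against 10% with 283 per arm, the loss is 0.25, 0.5 or 1.0 point of a 5-point excess at f = 5%, 10% or 20%. At f of 5% or less it is minor; at 10% to 20% it is worth seeing. The direction rests on unboosted men having the standard arm's risk. The size rests on f, which the article does not give, and on assumed toxicity rates. The documents do not support replacing ITT for toxicity.

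**What to change.** Keep ITT for efficacy, for quality of life and as the randomised comparison of toxicity. Add one sentence to the Data analysis section, for example: *Acute and late toxicity will also be compared by treatment actually received (boost delivered or not) among patients who started radiotherapy, and the number of experimental-arm patients given no boost will be reported.* Add the same comparison to the yearly statistical comparison of toxicity sent to the DSMB. Define in advance what counts as a delivered boost, since a yes/no split does not capture a boost given at a locally reduced dose.

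The cost is one sentence and one extra set of tables. The data look obtainable: the section on the first 50 patients says delivered doses to target and organs at risk were calculated for each patient. The drawback is that the treatment-received comparison is not protected by randomisation, so it should be read beside the ITT result and not in its place.

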**Methods/Design:**

The FLAME-trial (**F**ocal **L**esion **A**blative **M**icroboost in prostat**E **cancer) is a single blind randomized controlled phase III trial. We aim to include 566 patients (283 per treatment arm) with intermediate or high risk adenocarcinoma of the prostate who are scheduled for external beam radiotherapy using fiducial markers for position verification. With this number of patients, the expected increase in five-year freedom from biochemical failure rate of 10% can be detected with a power of 80%. Patients allocated to the standard arm receive a dose of 77 Gy in 35 fractions to the entire prostate and patients in the experimental arm receive 77 Gy to the entire prostate and an additional integrated microboost to the macroscopic tumor of 95 Gy in 35 fractions. The secondary outcome measures include treatment-related toxicity, quality of life and disease-specific survival. Furthermore, by localizing the recurrent tumors within the prostate during follow-up and correlating this with the delivered dose, we can obtain accurate dose-effect information for both the macroscopic tumor and subclinical disease in prostate cancer. The rationale, study design and the first 50 patients included are described.

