### Patients

Men with histological proven intermediate or high risk adenocarcinoma of the prostate, who will receive external beam radiotherapy using optimal position verification with implanted fiducial gold markers, are eligible for the study. Intermediate or high risk is defined according to the currently internationally accepted criteria from Ash *et al*. [21]. Intermediate risk is defined as patients having one factor of stage T2b-c, or Gleason score = 7, or initial prostate-specific antigen (iPSA) = 10-20 ng/mL. Patients having more than one of these factors or having stage T3, or Gleason score >7, or iPSA > 20 ng/mL are defined as high risk. Patients with low risk tumors are not included in this study, because the treatment outcome for this group is already excellent with a 10-year prostate cancer-specific survival approximating 95% [1].

Exclusion criteria are: previous pelvic irradiation, previous prostatectomy, World Health Organization (WHO) performance score > 2 [22] (= symptomatic, >50% during the day in bed, but not bedbound (score 3) or bedbound (score 4)), International Prostate Symptom Score (IPSS) ≥ 20, transurethral resection of the prostate (TURP) within 3 months from start of the treatment, general contraindications for MRI (i.e. cardiac pacemaker, metal implants or history of severe allergic reaction after administration of contrast agent) or the use of anti-coagulants that cannot be discontinued for the gold markers implantation.

The study protocol is approved by the Medical Ethical Committees of the participating hospitals. Written informed consent will be obtained from all patients.

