### Randomization

Randomization is performed by an independent trial center. If a patient meets the inclusion criteria and has provided informed consent, the physician contacts the trial center. To prevent randomly occurring differences in important prognostic factors across the two randomized groups, the randomization is stratified by TURP, hormonal treatment and by centre. A TURP prior to radiotherapy is associated with significantly more late genitourinary toxicity [23,24]. The likely mechanism of increased late toxicity is related to the relative devascularisation of the urethra after TURP and the decreased capability of the mucosa to repair sublethal damage after radiotherapy [24]. Hormonal treatment is a prognostic unfavorable factor for late genitourinary side effects [23,25] and erectile impotence [26-28]. Furthermore, a protective effect for hormonal treatment is reported for acute gastrointestinal side effects [23,29,30]. To prevent small numbers of patients in a particular hospital from all receiving, by chance, the same treatment, the hospital is chosen as one of the factors for stratified randomization as well.

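### Prespecifying the randomisation strata and baseline risk factors in the primary Cox model would gain efficiency from data already held; the two-arm comparison described is valid without them

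*Protocol article*

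**What the plan says.** Data analysis states that "Cox proportional hazards regression will be used to analyze differences in biochemical failure and disease-specific survival between the two treatment arms". It mentions no strata or covariates for this model and does not call the model unadjusted. The same section names an analysis of covariance for quality of life.

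Sample size considerations rests on "A one-sided log rank survival power analysis". The assumed effect is given as "64% and 74% free from biochemical failure after 5 years, in the control arm and experimental arm, respectively". The operating target for that effect is stated as "with a power of 80% at a one-sided 5% significance level". No covariates are mentioned here either.

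Under Randomization, "the randomization is stratified by TURP, hormonal treatment and by centre". The reasons given for TURP and hormonal treatment concern side effects. The reason for centre is to keep a small hospital from having, by chance, only one arm.

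The Patients section uses T stage, Gleason score and initial PSA (iPSA) to define risk. Its rule for the upper of the two eligible categories reads: "Patients having more than one of these factors or having stage T3, or Gleason score >7, or iPSA > 20 ng/mL are defined as high". These three factors are needed for eligibility and are tabulated for the first 50 patients in Table 1.

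**The concern.** The factors that the article uses to define risk enter neither the allocation nor the primary model as described. The Background gives freedom from biochemical failure of about 95% in low-risk patients and 60 to 75% in intermediate- and high-risk patients, so it treats these factors as closely tied to the endpoint. Low-risk patients are excluded, so that contrast overstates the spread within the trial. Table 1 still shows a mixed population: Gleason 4-6, 7 and 8-10 in 28%, 34% and 38%, and long-term hormonal therapy in 52%.

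When baseline factors predict the outcome, a Cox model that omits them estimates a hazard ratio closer to 1 than the model that includes them, with little difference in standard error. An analysis that does not account for the strata used in allocation also tends to have a standard error slightly too large. At stake is some power that costs no patients, and protection against covariates being chosen after results are known.

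**Working it through.** **1. The plan's own figure.** Inputs from the article: 283 per arm; 64% and 74% failure-free at 5 years; one-sided 5%; "accrual period of 5 years, 50% of the enrollment is complete when 70% of the accrual time has past"; 3.5 years of follow-up after the last entry; 20% lost over 5 years. Assumed here: exponential survival and loss, and exponentially rising entry over the 5 years.

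- Hazards: -ln(0.64)/5 = 0.0893 and -ln(0.74)/5 = 0.0602 per year. HR = ln(0.74)/ln(0.64) = 0.675.
- Loss rate: -ln(0.80)/5 = 0.0446 per year.
- For hazard λ, loss rate η and follow-up τ, the event probability is λ/(λ+η) × [1 - exp(-(λ+η)τ)]. Averaged over entry times it is 0.333 (control) and 0.241 (experimental), giving 162.6 expected events.
- Schoenfeld power: Φ(√(162.6/4) × |ln 0.675| - 1.645) = 80.6%.
- Freedman power: Φ(√162.6 × (1 - 0.675)/(1 + 0.675) - 1.645) = 79.7%.
- Events required for 80%: 160 (Schoenfeld) or 164 (Freedman), so N = 557 or 571 against the stated 566.

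The stated 80% is reproduced with no adjustment.

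**2. Simulation of the alternatives.** There were 3,000 trials per scenario (Monte Carlo SE about 0.7 points for power and 0.4 for type I error), with permuted blocks of 4 within TURP × hormonal treatment × centre. The mix follows Table 1: TURP 20%, hormonal therapy 52%, Gleason 28/34/38%, T3 or T4 78% (76 + 2). Assumed: four centres with small effects, independent factors, and TURP HR 1.0. In every scenario the marginal 5-year rates were held at 64% and 74%.

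The article gives no prognostic hazard ratios, so a range was assumed:

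| Scenario | Hormonal treatment | Gleason, per category | T3 or T4 | iPSA, per SD |
|---|---|---|---|---|
| None | 1.0 | 1.0 | 1.0 | 1.0 |
| Modest | 0.7 | 1.3 | 1.3 | 1.2 |
| Moderate | 0.5 | 1.6 | 1.5 | 1.4 |
| Strong | 0.4 | 2.0 | 2.0 | 1.6 |

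Power (%) at the design effect, and one-sided type I error (%) of the unadjusted model:

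| Scenario | Unadjusted | Stratified | Strata as covariates | Strata + risk factors | Type I error, unadjusted |
|---|---|---|---|---|---|
| None | 81.2 | 80.5 | 81.7 | 81.4 | 5.0 |
| Modest | 81.3 | 80.9 | 81.5 | 82.6 | 4.8 |
| Moderate | 82.2 | 82.6 | 83.5 | 86.8 | 4.2 |
| Strong | 82.3 | 83.4 | 84.1 | 90.5 | 4.4 |

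**3. Reading the tables.**

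- Strata alone: the change runs from 80.5 - 81.2 = -0.7 to 84.1 - 82.3 = +1.8 points.
- Strata plus risk factors: from 81.4 - 81.2 = +0.2 to 90.5 - 82.3 = +8.2 points.
- The gain comes from the estimate. In the strong scenario the average HR is 0.670 unadjusted and 0.624 adjusted, while the mean SE is 0.160 and 0.162.
- The unadjusted model's mean SE exceeds the empirical SD by about 1 to 4%, which fits its slight conservatism.

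**4. Chance imbalance.** With 38% Gleason 8-10 and 283 per arm, the arm difference in that share has SD √(2 × 0.38 × 0.62/283) = 4.1 points, a 95% range of about ±8 points.

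**The case against.** The strongest objection is that the article is silent, and silence is not exclusion. A journal article condenses the full protocol, and the covariate list of a Cox model is commonly left to that document or to the SAP. This stands: the omission is not a fault in this document.

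A reader might infer three stronger things, and the documents support none of them.

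- *The plan ignores its strata.* The text neither names nor rules out adjustment.
- *The plan loses power it promised.* It promised 80% from a log-rank test with no covariates mentioned, and that test delivers it. With the marginal rates fixed at 64% and 74%, any attenuation is already inside the design effect: unadjusted power stays at 81 to 82% in all four scenarios.
- *The standard errors are invalid for the randomisation.* The deviation is small and in the conservative direction. It also concerns only TURP, hormonal treatment and centre. T stage, Gleason and iPSA are not strata, so omitting them creates no mismatch with the randomisation.

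It is also fair to object that the upper end of the gain is favourable: the simulated risk factors are perfectly measured and correctly modelled, and their strengths are assumed. Chance imbalance, for its part, is covered by the test's type I error. Adjustment improves precision in the trial at hand and does not repair a bias.

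What remains is that the comparison the article describes is less efficient than one using data it already holds. In the checks run, the full model lost no power even when the factors predicted nothing.

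**Conclusion.** This is an efficiency improvement and not an error. The two-arm comparison is valid, slightly conservative (one-sided type I error about 4 to 5%) and meets the stated 80% power. Accounting for the strata alone is worth about -1 to +2 points. Adding iPSA, Gleason and T stage brings the total gain to about 0 to 8 points. The direction is secure if these factors predict biochemical failure. The size rests on the assumed hazard ratios, the Table 1 mix from one centre's first 50 patients, and correct modelling of the factors. If the full protocol or SAP already prespecifies the covariates, the point is closed.

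**What to change.** Confirm that the SAP contains, or add before anyone choosing the model has seen outcome by arm, one sentence: the primary Cox model accounts for TURP, hormonal treatment and centre (small centres pooled by a stated rule) and adjusts for log iPSA, Gleason group and T stage, with the arm coefficient as the primary test. State whether the strata enter as covariates or as separate baseline hazards. The full model simulated here used covariates. Report the unadjusted log-rank test, Kaplan-Meier curves and 5-year difference beside it.

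The cost is that sentence. No patients are added, and the three risk factors are already needed for eligibility. The one downside is that the adjusted hazard ratio is a conditional effect, while the endpoint is the five-year freedom from biochemical failure rate. The 5-year difference must therefore be shown with it.
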